**Discussion:**

In view of the high prevalence of chronic pain among older adults and its adverse impacts, it is important to provide older adults with tools to control their pain. We propose the use of peer volunteers to enhance the effects of an integrated pain management program. It is expected that pain can be reduced and improvements can be achieved among older adults in the areas of physical activity, functional mobility, loneliness levels, happiness levels, and the use of non-pharmacological pain relieving methods. Using these results, we will assess the need to conduct a larger study with a randomized controlled design.

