Our research team conducted a search of databases (PubMed and ScienceDirect) to study the application of PVs in intervention programs for older adults in Hong Kong from 1998 to the present. Four studies were identified, and they have been shown to achieve positive outcomes. However, the programs studied were those for healthy living, coping with stress, post-discharge support, and physical activity [15-18]. No pain management programs involving PVs were found. PVs were chosen over other forms of social support as the Hong Kong population is aging and people are living longer. After retirement, some older adults are still enthusiastic about serving the community. Therefore, we will select the PVs from the Institute of Active Ageing (IAA), which is dedicated to promoting active aging and the view of older adults as important contributors to society. As the IPMP has already been validated and published, and its effectiveness has been established, the effectiveness of the IPMP among older adults is well understood; however, whether this effect will be extended with the use of PVs is unknown. Therefore, in the present study we will attempt to test only the effectiveness of an IPMP that will be sustained by PVs.

The aim of this study is to determine the feasibility of PVs in an IPMP for Hong Kong older adults with chronic pain. According to the literature, pain management programs range from 4 weeks to 8 weeks. As the previous 8-week IPMP has already been validated, in this study we would also like to examine the dose-response relationship of an IPMP with PVs (that is, the possibly nonlinear association between intervention duration and pain intensity score). Our objective is to run a pilot study for a future main study with a randomized controlled design. It is hypothesized that the implementation of an IPMP supplemented with PVs for older adults with chronic pain will lead to improvements in levels of pain intensity, functional mobility, physical activity, loneliness, and happiness, and in the use of non-pharmacological pain-relieving methods.

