#### Data analysis

The IBM-SPBB version 20 will be used to perform a statistical analysis. Descriptive statistics (frequency, %), mean (standard deviation)) will be used to describe the demographic data of the participants.

To determine the dose-response relationship of this intervention program on pain, a generalized estimating equation with quadratic and higher order terms will be used. To examine the intervention effect, a t-test will be used to compare the mean pain intensity, functional mobility, physical activity, loneliness and happiness levels, and use of non-pharmacological methods collected at four time points, that is, between P0 and P1, P1 and P2, P1 and P3 (for pain only), and between P0 and P2, P0 and P3, and P2 and P3 (for other variables). The Kolmogorov-Smirnov normality test will be used to examine the normality of the outcome variables. If the data do not follow a normal distribution, we will use the Wilcoxon Signed-rank test and the Mann-Whitney U test for within-group and between-group comparisons, respectively. A *P* value of <0.05 will be considered statistically significant. An intention-to-treat analysis will be conducted for any missing data. All data from the ‘I can do it’ booklet will be gathered and used to calculate the participation rate.

The questionnaires for the volunteers will be compared using the McNemar test and a pair sample t-test for quantitative data. Qualitative data will be analyzed using content analysis [31]. Sentences or parts of sentences will be identified as meaningful units in each questionnaire. The meaningful units will be categorized into themes related to the perception of program. The themes will be compared and discussed to establish the credibility of the interpretations.

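### Pain is the sole primary outcome, but three co-equal contrasts test it at P<0.05 and none is named as deciding; the same rule covers 15 secondary contrasts

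*Protocol article*

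**What the plan says.** Under Primary outcome, the protocol article names pain intensity on the 0-10 numeric rating scale; the other measures stand under Secondary outcomes. Under Data analysis, the intervention effect is examined by this method: "a t-test will be used to compare the mean pain intensity" and the other outcomes between time points. The contrasts are:

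- Pain: "between P0 and P1, P1 and P2, P1 and P3 (for pain only").
- Other variables: "between P0 and P2, P0 and P3, and P2 and P3 (for other variables"). These variables are "functional mobility, physical activity, loneliness and happiness levels, and use of non-pharmacological methods".

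One threshold follows for everything: a P "value of <0.05 will be considered statistically significant". The section gives no order among the three pain contrasts and does not set any contrast apart as exploratory.

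The Procedure section defines P1 as the pain scores taken at the start of every session in weeks 1 to 8. With two sessions a week that is up to 16 scores per person, as the article's Discussion also says. Pain is recorded at P0, P2 and P3 as well.

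The Background hypothesis is that the programme "will lead to improvements in levels of pain intensity, functional mobility, physical activity, loneliness, and happiness, and in the use of non-pharmacological pain-relieving methods". The abstract adds: "Using these results, we will assess the need to conduct a larger study with a randomized controlled design".

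**The concern.** A named primary outcome limits error only if it comes with one deciding comparison. Here three comparisons have equal standing, so the pain result can be read from whichever is significant.

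They also answer different questions. P0-P1 compares baseline with scores taken during the programme. P1-P2 and P1-P3 compare those in-programme scores with weeks 8 and 12. If pain falls during the eight weeks, P1 already holds part of the fall, so the three tests have different true effects and can disagree. The comparison a reader would look for first, baseline against week 8 or week 12, is listed for every secondary outcome but not for pain.

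The same threshold then applies to 15 secondary contrasts. The results are meant to inform the decision about a larger randomized trial, and the hypothesis predicts improvement on all six outcomes. A nominally significant result would therefore be easy to present as evidence of improvement, with an error rate well above the stated 0.05.

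**Working it through.** The article gives no family-wise error rate, power or sample-size calculation, so there is no figure of its own to reproduce.

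**Inputs from the article.** 30 participants in a single group; threshold 0.05 per test; 3 contrasts on pain; 3 contrasts on each of 5 other outcomes.

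**Assumptions, not in the article.** Two-sided paired t-tests (sidedness is not stated), no true change, normal data, complete data, within-person correlation 0.5 over time, between-outcome correlation from 0 to 0.7. P1 is taken either as one score or as the mean of 16.

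**Count.** 3 + 5 × 3 = 18. From baseline: P0-P1 for pain, plus P0-P2 and P0-P3 for five outcomes, 1 + 10 = 11. Between later times: P1-P2 and P1-P3 for pain, plus P2-P3 for five outcomes, 2 + 5 = 7. Eighteen is a minimum, because physical activity has two sources (booklet and GPAQ) and the GEE terms come on top.

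**Pain alone.**
- Three independent tests: 1 − 0.95³ = 0.143 for any significant result; 1 − 0.975³ = 0.073 for a false improvement.
- All three contrasts share P1. If P1 is one score, they correlate at 0.5 in absolute value, and the chance of any significant result is about 0.125.
- If P1 is a mean of 16 scores, the correlation is (1/16)/(1 + 1/16) = 1/17 = 0.06, so the tests are nearly independent and the figure is about 0.14.
- Simulation agrees: 12-13% with a single score and 14-15% with the mean, so about 13-14%; a false improvement in about 7% either way.
- Against one test: 0.125/0.05 = 2.5 to 0.143/0.05 = 2.9 times for any result; 0.07/0.025 = 2.8 times for improvement.

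**All 18.** Independent tests give 1 − 0.95¹⁸ = 0.603 for any significant result and 1 − 0.975¹⁸ = 0.366 for a false improvement. Simulation with the contrasts as listed, over both readings of P1:

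| Between-outcome correlation | Any significant result | At least one false improvement |
|---|---|---|
| 0 | 55-56% | about 34% |
| 0.3 | 51-53% | 30-31% |
| 0.5 | 46% | 26-27% |
| 0.7 | 39-40% | 22-24% |

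Leaving out the five P2-P3 contrasts, which test maintenance after the programme, a false improvement has a chance of 17-27%. Raising the within-person correlation to 0.8 (checked at between-outcome correlation 0.3) gave 51% and 31%, so that assumption matters little.

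**After the fix.** One pre-named pain contrast has error 5% two-sided, or 2.5% for a false improvement.

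**The case against.** The strongest reply is that this is a pilot. The abstract says it aims to explore effectiveness, the Background and Discussion give feasibility as the aim, and pain is already the sole primary outcome with the rest labelled secondary. Multiplicity rules for secondary outcomes are commonly left to an analysis plan, which is not shown. The threshold is a nominal per-test level, and each test does have its 5%. No sentence says that one significant result would show the programme works.

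Much of this stands. It is why the secondary contrasts carry less weight here, and it rules out several stronger readings that a reader might infer:

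- *A false improvement has a 40-56% chance.* That is the chance of any significant result, worsening included. Reaching that range for improvement would need one-sided tests at 0.05, which the article does not state.
- *All 18 are before-after tests.* Only 11 start from baseline.
- *There is no hierarchy and no exploratory framing.* There is a primary outcome, and the study as a whole is described as exploratory. What is missing is an order among the pain contrasts and any such label in the analysis section.
- *Any one of 18 results decides.* The hypothesis joins its six outcomes with *and*, and the abstract attaches no P value to the decision on a larger trial.

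What the reply does not reach is the primary outcome. The article itself lists three pain contrasts as tests of the intervention effect and gives them one threshold. That is a rule stated badly, not merely a detail held back for another document, and the pilot label does not say which contrast counts.

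**Conclusion.** The point holds for the primary outcome and, with less weight, for the secondary outcomes. Followed as written, the plan leaves the pain result open among three tests, with about a 13-14% chance of a significant result when nothing has changed and about 7% for a false improvement, against 5% and 2.5%. These pain figures hardly depend on the assumed correlations or on how P1 is summarised.

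The figures over all 18 contrasts (about 40-56% for any result, about 22-34% for a false improvement) depend on the assumed between-outcome correlation and measure how loosely one could read the results, not a decision rule that the article adopts.

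The change is worth making but does not threaten the study. Error control would not make this trial confirmatory in any case: in a single group of 30 without a control, regression to the mean and time trends remain whichever contrast is chosen.

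**What to change.** In Data analysis:

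1. Name one pain contrast, before the data are seen, as the single primary comparison. Baseline against one follow-up visit is preferable, for example P0-P2, because it is easy to interpret, does not depend on how the P1 scores are summarised, and uses pain scores already scheduled. Picking one of the three listed contrasts would leave pain without a baseline-to-follow-up comparison.
2. Limit the P<0.05 sentence to that contrast.
3. Report the other pain contrasts, the secondary outcomes and the GEE terms as exploratory mean changes or estimates with 95% confidence intervals, without claims of significance. This fits the stated pilot aim and makes a correction such as Bonferroni over 18 tests (0.05/18 = 0.0028 each) unnecessary.

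The cost is a few sentences, with no new data or participants. The downside is that nominally significant secondary results can no longer be presented as established improvements.

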## Discussion

The 8-week group-based IPMP has already been validated and published, and its effectiveness has been established. Interventions that include some type of social support have great potential to increase participation and adherence, raising the question of whether the effects of an IPMP can be extended with the use of PVs. This study is aimed at evaluating the feasibility of using PVs in an IPMP for Hong Kong older adults with chronic pain.

This pilot study helps older adults to control their pain by providing a PV to encourage and accompany them. The limitations of this study should be noted. As it is only a pilot study lasting 12 weeks, long-term changes in the outcome measures cannot be evaluated. Moreover, there may be a ‘learning effect’, which will familiarize the participants with measuring instrument in the study as there will be a repeated measure of pain intensity in the beginning of all 16 training sessions. This study provides evidence for future, larger studies that utilize a randomized controlled design and a possibly longer follow-up time to adjust this ‘learning effect’ and to investigate whether PVs should be integrated in programs for older adults with chronic pain. This will help to promote health among older adults in the long term.

## Trial status

This study is currently in the process of recruiting participants. The study is expected to start in March 2014.

## Abbreviations

GPAQ: global physical activity questionnaire; IAA: Institute of Active Ageing; IPMP: integrated pain management program; MVPA: moderate-to-vigorous physical activity; NRS: numeric rating scale; PEP: physical exercise program; PVs: peer volunteers; RA: research assistant.
